### Plans to promote participant retention and complete follow-up {18b}

In cases where participants are hard to reach for follow-up, the research assistant performs repeated attempts to establish contact and document used strategies and the outcome. If contact is not successful over a period of three months, the follow-up will stop.

In the event of premature withdrawal from the trial, previously collected data will be included in the evaluation if the participant does not object this procedure.

### Data management {19}

Data is being collected using a paper–pencil based case report form (CRF) during the assessment and is then transferred by the research assistants to an electronic case report form (eCRF) in REDCap run on a secured server provided by the Clinical Trial Office at Charité Berlin Institute of Health (Charité BIH).

Data collection, analysis, and publication will be done using a project-generated identification (ID). The lists linking the IDs with the participants are stored separately from the data. Only the project coordinator and those who have been given access for organizational reasons have access to the link. Quality of data is promoted by range, validity, and consistency checks. Implausible or missing data can be corrected after consultation with the project manager.

### Confidentiality {27}

The study is adhering to the principles of the Helsinki Declaration and monitoring will be performed according to the guidelines on Good Clinical Practice (GCP) by the International Council for Harmonisation of Technical Requirements for Pharmaceuticals for Human Use (ICH). Data collection, analysis, and publication will be done using a project-generated ID. The lists linking the IDs with the participants are stored separately from the data. Only the project coordinator and those having been given access for organizational reasons have access to the link. The study is conducted in accordance to regulatory requirements of the local ethics committees of the involved sites.

### Plans for collection, laboratory evaluation, and storage of biological specimens for genetic or molecular analysis in this trial/future use {33}

N/A. Biological specimens are not collected.

## Statistical methods

### Statistical methods for primary and secondary outcomes {20a}

#### Primary outcome

Confirmatory analysis will be conducted based on the intention-to-treat (ITT) principle. The primary efficacy aim is to show that the percentage of participants who participate steadily over at least 50% of the 12-month follow-up in competitive employment and/or mainstream education is higher in the intervention group than in the control group. A logistic regression model adjusted for study site will be applied with a 95% confidence interval for group comparison. The two-sided significance level is 0.05.

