In the present trial, we investigate the effects of Supported Employment (SE) following the IPS model, which focuses on obtaining competitive work through improvement of functioning and vocational recovery in people with early psychosis [16, 17]. Furthermore, since many adolescents or young adults with early psychosis are still in secondary education, the IPS model is extended to achieve mainstream education: Supported Employment and Education – SEE [18]. There is strong evidence, that SE in adults with severe mental illness (SMI) leads to much higher rates of competitive job acquisition, increased working hours per week, and higher wages compared to general rehabilitation services [19–21]. Secondary education, SE, and competitive employment correlate positively with clinical, social, and economical outcomes as well as with quality of life [22–24]. Competitive employment is defined as jobs that anyone can apply for regardless of disability status. Mainstream education is defined in accordance with the Organization for Economic Cooperation and Development (OECD) [25] as educational programs leading to a qualifying degree and open to the general public. In Germany, this includes the following educational settings: secondary education (“sekundärer Bildungsbereich”), education examinations, internships (e.g., “Praktisches Jahr”), apprenticeship that generally lasts for 2 to 3 years and enable people to carry out a professional activity (“Berufsausbildung”), and higher education (university, university of applied sciences). Vocational education programs in line with traditional vocational rehabilitation (TVR) approaches following the “first train – then place” approach do not account as mainstream education [18].

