### Eligibility criteria {10}

Inclusion criteria are [1] adolescents and young adults aged between 16 and 35 years with [2] a clinical diagnosis of early psychosis. The latter is being defined in accordance with the largest trial of early intervention in psychosis worldwide so far (*n* = 404; [6]): SEEearly participating patients have to fulfill the DSM-5 (Diagnostic and Statistical Manual of Mental Disorders, volume 5) schizophrenia spectrum criteria or other psychotic disorder criteria. In addition, the onset of the first episode of psychosis should not be longer than 5 years ago or initial presentation to mental health services due to psychotic symptoms was within the last 5 years. Structured Clinical Interview for DSM-5 (SCID), Modules B and C, is used to confirm diagnoses according to the DSM-5. Further inclusion criteria are [3] general interest in competitive employment and/or mainstream education and [4] sufficient German language abilities (≥ A2). Exclusion criteria are [1] learning disability or mental retardation, [2] insufficient German language abilities (< A2), and [3] physical or organic handicap that seriously impedes work or educational functioning.

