## Sample size {14}

The sample size calculation was based on the primary dichotomous outcome “*steady participation for at least 50% of the 12-month follow-up period in competitive employment and/or mainstream education*” as used in prior studies [22, 32, 38]. Here, the reported steady participation in competitive employment rates vary between 44 and 39% for IPS vs. 11 and 23% for TAU. To detect differences of 24% between the two groups and 40% in the IPS arm vs. 16% in the control arm, the required sample size to find a significant effect with a power of 0.9 at a two-sided significance level of 0.05 is given by 144 participants (72 per arm). The sample size calculation is based on a *χ*^2^-test. As the logistic regression model adjusted for the study site which is used for the primary efficacy analysis yields a power increase compared to the *χ*^2^ test (i.e., the latter ignores the influence of study site effects), this strategy for sample size calculation defines a conservative procedure. The power calculation was performed using NQuery Version 8.4.1.0. Published drop-out and lost to follow-up rates in SE and SEE trials range from 5% [39] to 30% [27]. In a pilot RCT at the study center Berlin I, the drop-out rate was 22%. Assuming a drop-out rate of 22%, the total number of participants to be recruited is thus 184.

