## Data collection and management

### Plans for assessment and collection of outcomes {18a}

Comprehensive baseline assessment and 6 and 12 months of follow-up assessments are done face-to-face or, if not possible, via video-calls by a research assistant. Each research assistant has completed a specific training prior to the start of the trial. Monthly assessment of the primary outcome, current medication, and psychiatric treatment is done face-to-face, via video-calls, or telephone. Loss of masking of treatment allocation is being documented. The reliability and validity of assessments will be examined. The baseline assessment includes diagnoses according to ICD-10 (International Statistical Classification of Diseases and Related Health Problems, version 10) and DSM-5, sociodemographic information, including education/employment and housing situation, psychiatric treatment prior to the trial, and motivation for change regarding employment/education. Furthermore, we will use the following validated questionnaires to assess mental health status, substance use, and quality of life at baseline and the follow-ups:*Psychopathology* will be measured with the well-established observer-rated Positive and Negative Syndrome Scale (PANSS; [40]). This scale is widely used and known as the “gold standard” for psychopathological outcomes of interventions in people with psychotic disorders [41].*Functional impairment* with regard to occupational activity and participation will be assessed due to its tight connection to the aim of SEE. This will be realized by observer ratings on the short version of the International Classification of Functioning, Disability, and Health (Mini-ICF-APP) instrument. This widely applied instrument is used to quantify disability [42] and allows for comparing results of the presented trial with other RCTs [43]. As a global assessment to measure functionality and to ensure comparability with other studies, we also use the Global Assessment of Functioning (GAF; [44]).*Substance use* history and past month substance use will be measured by a modified version of the Addiction Severity Index (ASI; [45–47]. Since the comorbidity of *cannabis use* and psychosis has been widely discussed, a German version of the Daily Sessions, Frequency, Age of Onset and Quantity of Cannabis Use Inventory (DFAQ-CU) will be used to specifically assess abuse of cannabis with a focus on frequency, age of onset, and quantity of consumption [48].*Subjective quality of life* will be measured with the WHOQOL-BREF [49], a short version of the WHOQOL-100 (World Health Organization Quality of Life scale). This self-rating instrument presents with high rates of internal consistency (*α* = 0.57 to *α* = 0.88) and is translated into 30 languages, which allows for comparison with international research results.Economic outcomes will be assessed in terms of *social return on investment* (SROI) at last follow-up after 12 months. This measure is designed to survey the value of social benefits created by a program in relation to the relative cost of achieving those benefits. SROI will be computed as the ratio of “benefits” to “total investment” for each participant and is expressed as percentage. Participants’ earnings in both competitive and non-competitive jobs, education, and apprenticeship hereby account as “benefits.” “Investments” are defined at the total vocational program costs per patient and total costs of mental health service [22, 50–52].

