### Methods for additional analyses (e.g., subgroup analyses) {20b}

Additional sensitivity analyses will be conducted for different populations (per-protocol population, participants with complete cases). Sub-group analyses will be conducted regarding participants’ status of mainstream education at baseline (interrupted mainstream education vs. not engaged in mainstream education).

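### The primary model leaves out baseline engagement in work or education, a probable strong predictor of the endpoint that is already recorded, and so gives up power and precision

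*Protocol article*

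**What the plan says.** - **Eligibility criteria {10}.** The only vocational requirement is "general interest in competitive employment and/or mainstream education". None of the three exclusions concerns current work or study.
- **Outcomes {12}, Primary outcome.** The endpoint is binary: steady participation for at least half of the 12-month follow-up. It does not require a new job or course to begin.
- **Plans for assessment and collection of outcomes {18a}.** Baseline data include "sociodemographic information, including education/employment and housing situation".
- **Statistical methods {20a}, Primary outcome.** "A logistic regression model adjusted for study site will be applied with a 95% confidence interval for group comparison". The aim is worded as a comparison of percentages.
- **Statistical methods {20a}, Secondary outcomes.** The sensitivity model adds age and gender.
- **Methods for additional analyses {20b}.** The subgroup analysis splits participants by baseline education status: "interrupted mainstream education vs. not engaged in mainstream education". Employment status is not used.
- **Sample size {14}.** Planning is on "40% in the IPS arm vs. 16% in the control arm", one overall rate per arm, "with a power of 0.9 at a two-sided significance level of 0.05".

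**The concern.** A participant who is enrolled or employed at entry and simply carries on can meet the endpoint under either treatment. Someone who starts outside work and education has to get in first and then stay. Status at entry should therefore separate successes from failures more sharply than age or gender, and probably more than site.

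The Sample size section argues that adjusting for site gains power over the chi-square test. The same argument applies to engagement at entry, and the variable is already in the data. Leaving it out means that chance differences between the arms in the share already engaged stay in the treatment comparison as noise.

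The subgroup split adds an interpretive gap. If engaged people enrol, they have no level in it, so the analysis cannot show whether an overall effect comes from new starts or from retention.

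**Working it through.** **1. The plan's own figure.** Inputs from Sample size {14}: 0.40 versus 0.16, two-sided 0.05, power 0.90, chi-square test.

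n per arm = [1.96·√(2·p̄(1−p̄)) + 1.2816·√(p₁(1−p₁) + p₂(1−p₂))]² / (p₁−p₂)², with p̄ = 0.28

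= [1.96·√0.4032 + 1.2816·√0.3744]² / 0.24² = (1.2445 + 0.7842)² / 0.0576 ≈ 71.5, so 72 per arm and 144 in total. Power at 72 per arm is 0.902. The stated size reproduces.

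**2. Inputs the document does not give.** The share f engaged at entry, taken as 10% to 30%. The success rate q among them, taken as 80% in both arms and varied from 70% to 90%.

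**3. Scenario A: 40% versus 16% applies only to those not engaged.** Overall rate per arm = f·q + (1−f)·r, with r = 0.40 or 0.16. For f = 20%: 0.16 + 0.8·0.40 = 0.480, and 0.16 + 0.8·0.16 = 0.288.

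| f | SEE vs TAU | Difference | Chi-square power, 72 per arm |
|---|---|---|---|
| 0% | 40.0% vs 16.0% | 24.0 | 0.90 |
| 10% | 44.0% vs 22.4% | 21.6 | 0.79 |
| 20% | 48.0% vs 28.8% | 19.2 | 0.66 |
| 30% | 52.0% vs 35.2% | 16.8 | 0.53 (0.54 by exact enumeration) |

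Moving q to 70% or 90% changes power by no more than about 2 points. This table shows dilution of the effect. It is not the cost of leaving out a covariate.

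**4. The cost of leaving out the covariate, Scenario A.** Simulated trials: 72 per arm, six sites, likelihood-ratio test of treatment, 2,000 trials per row, engagement entered as a binary indicator.

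| f | Site only | Site + engagement | Gain |
|---|---|---|---|
| 10% | 0.79 | 0.84 | 5 points |
| 20% | 0.68 | 0.77 | 9 points |
| 30% | 0.55 | 0.66 | 11 points |

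A repeat simulation gave 0.79 to 0.85, 0.65 to 0.74 and 0.55 to 0.67, so the gain is about 5 to 12 points. Type I error was near 0.05 with either model.

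**5. Scenario B: 40% versus 16% holds overall.** Engagement is prognostic with an odds ratio of 5 to 15, f = 10% to 30%, and the treatment odds ratio is the same in both strata. Site-only power is 0.90 to 0.92. With engagement added it is 0.92 to 0.97.

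**6. Where the noise comes from.** With f = 20%, the standard deviation of the between-arm difference in the engaged share is √(2·0.2·0.8/72) = 0.067. Engaged participants succeed at 0.80, against an average of (0.40 + 0.16)/2 = 0.28 for the others. An imbalance of one standard deviation therefore moves the observed difference by about 0.067·0.52 = 0.035, or 3.5 points against a true 19.2. The site-only standard error already allows for this; adjustment would remove much of it.

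**The case against.** **The headline fall in power is not caused by the model.** This is right. The drop from 0.90 to 0.66 or 0.54 comes from assigning the planned rates to the non-engaged only, which the Sample size section does not do. If those rates hold overall, the site-only model keeps about its planned power. A reader might take the whole drop as the price of the site-only model, but steps 4 and 5 above do not support that.

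**The number of engaged participants is unknown and may be small.** This also stands. The Background remark that "many adolescents or young adults with early psychosis are still in secondary education" describes the wider patient population and explains why the intervention was extended to education. It is not a forecast of who will enrol. The subgroup levels suggest that the authors expected participants to be out of education at entry. But no stated criterion makes that so, and the levels say nothing about employment. If the full protocol does require participants to be out of work and education, the point falls away.

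**The site-adjusted analysis is valid.** Agreed. Randomisation and the stated error rate cover chance imbalance. A reader might infer that the omission biases or attenuates the effect. It does not: the odds ratio with and without the covariate are different targets, and the expected risk difference is unchanged.

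**The subgroup levels and the time-to-first outcome.** A reader might also call the two subgroup levels overlapping. Read ordinarily, a paused programme and no programme are distinct; only the missing currently engaged level matters. How time to first job or education treats people already engaged is detail that an analysis plan commonly settles.

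**Covariate choice is preference.** Partly. But the article names the covariates of both models and the subgroup levels, so this concerns a stated choice, and adjustment raised power in every scenario examined.

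**Conclusion.** The point holds as one of efficiency and interpretation; the validity of the primary test is not in question. On the stated criteria, people already in work or education may enrol and may succeed by continuing, yet their status is in neither model and has no subgroup level.

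The cost of the omission is about 5 to 12 points of power if 10% to 30% are engaged and 80% of them succeed in both arms. If 40% versus 16% holds overall, the plan keeps its intended power and forgoes a smaller gain. The shares, success rates and prognostic odds ratios are assumptions.

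Dilution is a separate matter. Under Scenario A adjustment brings power back to about 0.84 to 0.66, still short of 0.90. Engagement is best described as probably strongly prognostic. Calling it near-deterministic goes too far, since even the assumed rates are 80% against 16% to 40%.

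**What to change.** Before database lock, and without looking at outcomes by arm:

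1. Add a binary baseline indicator (currently in competitive employment or mainstream education: yes/no) to the primary logistic model alongside site.
2. Report the standardised risk difference from that model with its 95% confidence interval, because the aim is stated in percentages.
3. Add a currently engaged level, covering employment as well as education, to the subgroup analysis in {20b}.

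The cost is a short change to the analysis plan, using data already collected. There are two downsides. The odds ratio becomes conditional on one more covariate, which the risk difference offsets. The engaged level may also be sparse if few such people enrol, so a yes/no indicator is safer in the primary model than a three-level factor.

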#### Secondary outcomes

As a sensitivity analysis to the primary efficacy, a logistic regression model will be applied with additional covariates age and gender. Descriptive methods will be used for the analyses of the other secondary outcomes, including calculation of appropriate summary measures of the empirical distribution as well as 95% confidence intervals and calculation of descriptive two-sided p-values.

### Safety

Safety analysis includes calculation of frequencies and rates of serious adverse events (SAE). Data will be analyzed using validated statistical software.

### Interim analyses {21b}

N/A. Interim analyses will not be performed.

### Methods for additional analyses (e.g., subgroup analyses) {20b}

Additional sensitivity analyses will be conducted for different populations (per-protocol population, participants with complete cases). Sub-group analyses will be conducted regarding participants’ status of mainstream education at baseline (interrupted mainstream education vs. not engaged in mainstream education).

### Methods in analysis to handle protocol non-adherence and any statistical methods to handle missing data {20c}

Efforts are made to follow-up participants who dropped out from treatment in order to collect outcome data to reduce missing and to detect underlying structures about missing data mechanisms (e.g., missing at random, MAR). Missing values will be imputed using multiple imputation chained equations (MICE; [56]).

### Plans to give access to the full protocol, participant level-data and statistical code {31c}

N/A. We do not plan to grant public access to the full protocol and statistical code. Participant-related data will not be shared at any point of the trial.

## Oversight and monitoring

### Composition of the coordinating center and trial steering committee {5d}

The project leader has regular contact (online or telephone) with project leaders of the involved sites in order to identify potential challenges. The transregional project coordinator supervises the project status and number of study enrollment of each site and holds monthly cross-site online meetings with the assessors and informs the project leader about the current status.

### Composition of the data monitoring committee, its role and reporting structure {21a}

An IDMC will supervise the trial and ensure adherence to the protocol. In case of unexpected, problematic events, they will be asked for advice whether to continue, modify, or stop the trial. It is not planned to conduct interim statistical data analyses while the trial is ongoing.

Further information about names and affiliation of the IDMC are available upon request.

### Adverse event reporting and harms {22}

All study participants are regularly monitored by SEE-specialists, trial staff, and further medical staff. Although there are no known adverse events (AE) or SAE, which have been described as associated with the experimental intervention, an independent expert board is established, which gives advice to the trial staff and monitors safety data. All SAE (e.g., severe worsening of symptoms, hospitalization, or suicidality) reported by the subject or observed by the investigators are documented and assessed to ensure a sufficient surveillance on the safety of the patients. SAE are events that are fatal or life threatening, require hospitalization, or result in persistent or significant disability or incapacity. These events do not necessarily have been caused by the study intervention. Patients must be observed after these events until symptoms have disappeared. SAE are documented in the patient’s chart and on a separate reporting form. They are reported to the coordinating investigator and to the IDMC. A safety surveillance system is established and follows the applicable legislation. Definition on SAE and all other safety information are used as defined by applicable law/guidelines and the protocol. The procedure will follow the standards and standard operating procedures (SOP).

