**Only intervention group (SEE)**													
Efficacy belief (JSSE-O)			x										
Work alliance (WAI-VR)			x										x
Documentation of the SEE-specialists		x	x	x	x	x	x	x	x	x	x	x	x

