## Interventions

### Explanation for the choice of comparators {6b}

In SEEearly, we compare TAU plus SEE (intervention) to TAU alone (control condition) in the respective recruitment centers for 12 months. TAU is defined as common multidisciplinary clinical practice for adolescents and young adults with early psychosis. This includes medical review, pharmacological treatment, psychosocial support including social work counseling, and referral to external government-funded vocational programs. Type and frequency of the psychosocial support interventions in the control condition is being documented. Pharmacological treatment is continuously assessed and the respective chlorpromazine equivalents are calculated. To standardize support regarding work and education across study sites and to make sure that employment and education is being addressed with participants of the TAU condition as well, all social workers involved with participants in the TAU condition are obligated to have at least one consultation with the participants regarding competitive employment and/or mainstream education. Participants of the TAU condition do not have access to SEE treatment during the time of the trial but will be offered IPS after completing the study, if available at the respective mental health service.

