### Intervention description {11a}

SEE is based on the nine IPS principles (SE and SEd [Supported Education]). IPS is an evidence-based practice for helping people with severe mental illness to gain and maintain competitive employment and/or mainstream education [16–18, 29]. SEE is delivered by SEE-specialists trained according to a standardized SEE manual [18], which has been translated into German in the preparation phase of the project. Every participant is being assigned to a SEE-specialist, who provides services based on the IPS principles. These include that (a) the SEE-specialist builds partnerships with employees and education program staff and provide follow-up support to both the employee and the employer once work is obtained and (b) the SEE-specialist is part of the mental health treatment team and is therefore located in the same office space and also attends and participates in client’s treatment teams using a shared case management and documentation system.

For the present trial, interventions take place for a duration of 12 months for each participant in the intervention group and range from engagement techniques (e.g., motivational interviewing) to individualized competitive employment and/or mainstream education searches and from experience-based assessment to benefits in counseling/work incentives planning. In cases where participants are hard to reach, SEE-specialists perform repeated attempts to establish contact and document used strategies and the outcome. If contact is not successful over a period of 3 months, the follow-up will stop.

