### Relevant concomitant care permitted or prohibited during the trial {11d}

All participants will receive TAU for adolescents and young adults with early psychosis in an outpatient psychiatric setting for the duration of the trial. Participants of the control group cannot receive SEE for the duration of the trial.

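### SAE detection may differ by arm: the harms section has SEE-specialists monitoring everyone, but elsewhere their ongoing contact is described only for the SEE arm

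*Protocol article*

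**What the plan says.** The section on adverse event reporting {22} names the observers: "All study participants are regularly monitored by SEE-specialists, trial staff, and further medical staff". It makes no distinction by arm. The same section gives the capture rule, under which SAEs "reported by the subject or observed by the investigators are documented and assessed", and the definition: "SAE are events that are fatal or life threatening, require hospitalization, or result in persistent or significant disability or incapacity". It also names severe worsening of symptoms and suicidality as examples, and sends SAEs to the coordinating investigator and the independent data monitoring committee (IDMC).

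Four other places bear on who is in regular contact with an SEE-specialist:

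- Choice of comparators {6b}: "Participants of the TAU condition do not have access to SEE treatment during the time of the trial".
- Concomitant care {11d}: "Participants of the control group cannot receive SEE for the duration of the trial".
- Intervention description {11a}: each SEE participant has an assigned specialist, and "interventions take place for a duration of 12 months for each participant in the intervention group".
- Table 1: the row "Documentation of the SEE-specialists" is marked for months 1 to 12 and sits in the block reserved for the intervention group.

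The only specialist contact with controls that is described is under Implementation {16c}, where specialists carry out the randomization and tell participants the result. The Safety section plans SAE frequencies and rates and states no between-arm test.

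**The concern.** If SAEs are found by report or observation, the yield depends on how many people are looking and how often. In the SEE arm, a named specialist who knows the allocation works within the treatment team for 12 months and makes repeated attempts to reach participants who are hard to contact. No counterpart is described for controls beyond usual care and the research assistant. Table 1 has no SAE row, so the article shows no scheduled enquiry that would even this out.

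The by-arm SAE rates are at stake. In a two-arm trial they will be read side by side even without a test, and the IDMC receives the reports as they come in. Extra detection in one arm would make SEE look less safe than it is. Events in controls that no one was placed to notice, suicidality in particular, might go unrecorded.

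**Working it through.** **Step 1: the sections side by side.**

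| Place | Regular specialist contact, SEE arm | Regular specialist contact, controls |
|---|---|---|
| Adverse events {22} | yes | yes (all participants) |
| Intervention description {11a} | yes, 12 months | not described |
| Comparators {6b}, concomitant care {11d} | – | no SEE during the trial |
| Table 1, specialist documentation | months 1–12 | none |
| Implementation {16c} | at randomization | at randomization only |

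Ongoing monitoring of controls by specialists is asserted once and supported nowhere else.

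**Step 2: channels open to both arms.** Both arms receive outpatient psychiatric usual care throughout {11d}. Both have monthly rater assessment of ongoing psychiatric treatment and medication (Table 1, {18a}) by research assistants who are to remain blind {17a, 17b}. Both have psychopathology and functioning ratings at 6 and 12 months. The monthly treatment item should reveal most psychiatric admissions. No scheduled item in Table 1 is aimed at suicidality or at non-psychiatric serious events, and the symptom ratings at 6 and 12 months are widely spaced.

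**Step 3: what the plan's own figures allow.** No SAE risk, detection rate or safety power is stated, so there is no plan figure on this point to reproduce. The only usable figure is the recruitment target: 184 participants allocated 1:1, or 184/2 = 92 per arm.

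**Step 4: illustration.** Let p be the true SAE risk, equal in both arms, and let s1 and s0 be the detection probabilities in the SEE and control arms. All three are assumptions.

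- Observed risk = p × s, for each arm.
- Spurious risk ratio = (p × s1)/(p × s0) = s1/s0, whatever the value of p.
- Spurious risk difference = p × (s1 − s0).

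| s1 / s0 | Risk ratio | Difference, p = 10% | Difference, p = 40% | Expected detected events per 92, p = 20% |
|---|---|---|---|---|
| 95% / 95% | 1.00 | 0 | 0 | 17.5 vs 17.5 |
| 95% / 90% | 0.95/0.90 = 1.06 | 0.5 points | 2 points | 17.5 vs 16.6 |
| 95% / 80% | 0.95/0.80 = 1.19 | 1.5 points | 6 points | 17.5 vs 14.7 |
| 95% / 70% | 0.95/0.70 = 1.36 | 2.5 points | 10 points | 17.5 vs 12.9 |

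The counts are 92 × 0.20 × s; for example, 92 × 0.20 × 0.95 = 17.5.

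**Step 5: how Step 2 limits the gap.** Suppose a share f of SAEs are psychiatric admissions found equally well in both arms. Then s1 − s0 = (1 − f) × (the detection gap among the remaining events). The larger the share of psychiatric admissions, the closer the trial lies to the top rows of the table. The documents give neither f nor the gap.

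**The case against.** The strongest defence has four parts.

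- **Shared observers.** A specialist adds only events that the participant, the treating clinicians and the blinded rater all miss. This stands for psychiatric admissions. It is weaker for suicidality without admission and for non-psychiatric events.
- **A collective reading.** The sentence in {22} may mean that these staff groups between them cover all participants. That would remove the contradiction in wording, but it would also confirm that the specialist watches one arm only.
- **A condensed article.** The harms section refers to the protocol, applicable guidelines and standard operating procedures, which are not shown and may already contain a scheduled SAE enquiry. This stands. The missing row in Table 1 is therefore not a defect in itself, and if such an enquiry exists, the main work left is to reconcile the wording.
- **Formal seriousness.** Severe worsening without admission will often fall outside the SAE definition. That narrows the gap, although the section itself lists worsening and suicidality as examples.

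A reader might infer more than the text supports:

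- *That the SAE rates will be biased.* With no detection rates given and several channels common to both arms, only the possibility can be asserted.
- *That a benefit on hospitalization will be hidden.* The abstract lists hospitalization as a secondary outcome, but nothing ties it to specialist reports. The nearest scheduled source is the monthly treatment item, which is the same in both arms.
- *That specialists must be contaminating the control arm.* The exclusions in {6b} and {11d} concern receiving SEE. Noticing a safety event does not amount to delivering it.
- *That controls never meet a specialist.* They do, at randomization.

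**Conclusion.** The point holds as a risk of unequal ascertainment that the text leaves open. The statement in {22} does not fit {6b}, {11a}, {11d} and Table 1. Under a capture rule based on report or observation, the SEE arm appears to have an additional unblinded observer. Any resulting distortion would run against SEE, as an apparent excess of SAEs.

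Its size cannot be derived from the document. The spurious risk ratios of 1.06 to 1.36 rest wholly on equal true risks and on assumed detection of 95% in the SEE arm against 90% to 70% in controls. Since psychiatric admissions should be found in both arms, the gap may be small overall and concentrated in the event types named in Step 2. The primary outcome analysis is not affected. This is a cheap improvement worth making.

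**What to change.** 1. Reconcile {22} with {6b}, {11a}, {11d} and Table 1, so that the article states which staff monitor which arm. The sponsor must say which description is true; the document does not settle it.
2. Unless the full protocol already does so, add a short SAE enquiry to the existing monthly rater contact, worded identically in both arms and phrased so as not to invite disclosure of allocation.
3. Record the detection source of every SAE on the existing reporting form.
4. Present by-arm SAE rates primarily from sources equally available in both arms: monthly contact, clinical chart and death notification. Show all SAEs alongside, including those reported only by a specialist, and send all of them to the IDMC.

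The primary presentation should not be limited to events found at rater contacts. Deaths cannot be self-reported, and follow-up stops after three months without contact {18b}, so events in unreachable participants would be lost.

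The cost is a slightly longer monthly call and one extra field on the SAE form. No new visit or staff is needed.
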